### Medical Literature and Evidence-Based Medicine

Access to large data sets is key to training the AI algorithms needed to deliver the promise of DTs and personalized medicine. Data sets needed for training include well-designed clinical trials for decision support, risk assessment tools that can provide feedback on treatment interventions and large observational cohorts for phenotyping of diverse populations, and prediction of response to interventions. The “All of Us” research program funded by the National Institutes of Health is one example of a data set that could be used to develop a DT infrastructure. With a stated goal of collecting data from a million highly diverse groups of participants, the project will provide considerable biopsychosocial data that advance the goal of personalized medicine [52-54].

The last few decades have seen rapid advances in understanding the pathophysiology of the majority of diseases and the development of new treatment options. The “bench to bedside” process has relied on RCTs of varying designs to obtain needed approval for any recommended clinical treatment. RCTs typically rely on the recruitment of homogenous populations of potential responders to determine the efficacy of a medication or an intervention. RCTs have become the gold standard for evidence-based medicine; however, clinicians treat heterogenous patient populations who often do not share the characteristics of participants found in RCTs. Diseases do not often present with identical symptoms from one patient to another. Treatment response and side effects can also vary greatly from one person to another. Because of this, personalized medicine has been embraced as a way to improve the care of the individual patient. This approach seeks to tailor treatment to each person to account for genetic, physiological, biochemical, behavioral, and environmental differences [24,55]. To be most effective, personalized medicine requires the consideration of a large number of variables. The results from traditional RCTs do not easily lend themselves to providing the needed information to practice evidence-based personalized medicine [17,56].

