### Designing and Developing a DT for NCDs

To our knowledge, a protocol designed to assess the use of a DT to treat NCDs has not been conducted or reported in scientific literature. As noted above, NCDs are lifestyle diseases that can require a multidisciplinary approach toward effective diagnosis and behavior change to impact the long-term reversal of health risk factors using a biopsychosocial approach. The interdisciplinary approach needed to effectively treat a patient with an NCD requires the following:

Comprehensive medical review and treatment of the consequences of the NCD.Biopsychosocial evaluation with risk assessment that can impact treatment goals.Psychological assessment and comprehensive treatment when needed.Modification of behaviors that have led to the development of the NCD.Evaluation of current activity, presence, and/or treatment of pain, and integrated rehabilitation when identified.

The design and implementation of a DT for an NCD is as follows:

Conduct a literature review of appropriately designed studies related to any particular NCD. These studies will provide an analysis of health risks and therapeutic clinical trials that include both health risks and responder analyses. This information will be used through supportive AI decision-making to form a DT and to offer clinical support.Obtain a patient-centered interface that connects with an electronic medical record to collect existing data. This will allow for the assessment of the patient’s baseline key health indicators, to track key variables to be used to update the patient’s DT while providing feedback, including contextually specific motivational messaging, and to support the provider. Identification of patient engagement issues and possible measures of treatment outcomes would be generated. Tracking of key patient measures will be facilitated by peripherals enabled to gather objective data such as blood glucose, blood pressure, daily activity, oximetry, and weight [77].The computational process will begin and continue throughout the study process as data are collected, and the patient status is defined by analyzing key health data to form both the initial and updated individual DT using a biopsychosocial framework.Collect deidentified data that will further refine the algorithms used to create the DT and future DTs.

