If the risk factors are confirmed, an additional evaluation will be used to determine other specific risk factors associated with that condition, including level of physical activity, psychological traits or maladaptive behaviors, and barriers to improvement, including the presence of pain, sleep disruption, smoking, and other comorbidities related to worsening health. For an overview of these inputs, refer to Table S2 in Multimedia Appendix 1. These secondary domains will become the individual’s study-specific targets. All of these factors will be incorporated into the participant’s DT. The DT will be shared with the patient through the study app and reviewed with the patient during an in-person follow-up visit. The study platform will provide daily questionnaires that are specific to each NCD category and problem list. Objective tracking of the patient’s activity level and physiological measures (such as blood pressure, glucose levels, and pulse oximetry) will continue throughout the treatment period. All these daily data points will be used to update the DT and will appear in the participant’s study portal that is part of the patient-facing app. The updated DT primary endpoint will reflect the change in health risk. Participants found not to be compliant with the program will be contacted and interviewed regarding barriers and their impressions of the program. Clinician decision-making will also be tracked. Variance from DT treatment recommendations and the impact on NCD risk factors will be reviewed and statistically compared to expected outcomes from relevant evidence-based literature.

Automated contextual daily motivational messaging that aligns with the participant’s behavioral traits will continue throughout the study period. Daily compliance reminders for medication regimens will be incorporated into the study app. The program goal will be a 37% reduction in long-term health risk from baseline as determined by the NCD-specific risk questionnaire (Tables S1 in Multimedia Appendix 1). This is considered to be a meaningful reduction in health risk using the financial modeling included in this reference that will sustain a DT program [93]. The number of participants in each arm reaching this goal will be used to evaluate the primary objective of this study as noted above. Each candidate will be followed for 6 months, and the study length will be determined by enrollment rate.

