#### Enrollment Procedures

The smartphone will be used to communicate with the eligible participants. They will be sent a poll using an SMS text messaging–based survey app for eligibility for in-person evaluation. The administrative portal will automatically categorize participants into a defined level of risk of their NCD. The participants with confirmed NCDs will be evaluated by the interdisciplinary team noted above, and a personal treatment regimen will be designed for them to reduce their health risks, along with a DT that reflects their state of health at enrollment. There will also be a comparison-matched group of participants who will be randomized to a treatment-as-usual condition, where they will not have access to the DT technology. After sufficient instruction, the participants in the experimental treatment condition will be tracked daily and be provided with reinforcing messaging and automated problem-solving based on their DT. Any changes in their health-related behaviors will automatically be reflected in an updated DT. Efficacy of the DT and personalized medicine approach will be measured by the number of individuals reaching a 37% risk reduction, with comparison between enhanced care using the DT and treatment as usual (TAU). TAU is defined as the treatment of one of the study’s NCDs using published guidelines and literature as a guide, but without using any of the DT study interventions. Secondary outcome measures that will be tracked will include each of the diagnosed NCD risk factors and other outcome measures, including compliance and helpfulness ratings of the participants and treating providers. In addition to studying the 3 NCDs noted above, we will select patients diagnosed with type II diabetes with pain for further in-depth analysis, as detailed in the Statistical Methods section.

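### The side analysis of clinician departure from DT advice is to be tested against literature expectations, a benchmark that mixes case mix and background care with the effect of departing

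*Protocol article*

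**What the plan says.** Methods, Validation Methodology for a DT NCD, states that clinician decision-making will be tracked and then commits to an analysis in which departures from DT advice, and what they do to the NCD risk factors, are to be "statistically compared to expected outcomes from relevant evidence-based literature". It does not give the form of test, the benchmark values, the number of departures expected or a significance level. The Statistical Methods section does not return to it.

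Three other parts of the article bear on the benchmark:

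- Introduction, Medical Literature and Evidence-Based Medicine, says that "clinicians treat heterogenous patient populations who often do not share the characteristics of participants found in RCTs". The Discussion (Principal Findings) adds that eligibility was deliberately set so that the sample resembles real-life NCD patients.
- Introduction, Designing and Developing a DT for NCDs, says of the literature on health risks and clinical trials: "This information will be used through supportive AI decision-making to form a DT and to offer clinical support". The section on the elements needed to construct the DT likewise describes the virtual patient as a synthesis of patient evaluation and literature-based algorithms.
- The efficacy comparison is separate. On the 37% risk-reduction goal: "The number of participants in each arm reaching this goal will be used to evaluate the primary objective of this study". Enrollment Procedures sets DT care against TAU on the same goal and adds: "Secondary outcome measures that will be tracked will include each of the diagnosed NCD risk factors and other outcome measures".

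**The concern.** A statistical comparison with published outcomes is valid only if, absent any effect of the clinician's choice, these patients would have had the published outcomes. The article gives reasons to doubt that. It argues that trial participants are unlike practice patients, and it recruits practice patients. Differences in severity, comorbidity or background care would then show up as if they were consequences of following or departing from DT advice.

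The benchmark is also not independent of the thing being judged. Advice derived partly from the literature is assessed against expectations derived from the literature.

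What is at stake is modest but concrete. One secondary objective is to refine the algorithms that support clinical decisions. A spurious finding that departures help or harm could feed directly into that refinement.

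**Working it through.** **1. The plan's own related figure.** The only stated sample size that can be checked belongs to the DT versus TAU comparison of the Patient Global Impression of Change (PGIC): difference 0.6, SD 1.0, 85% power, two-sided 0.05 (Statistical Methods).

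n per arm = 2 × (1.960 + 1.036)² × 1.0² / 0.6² = 49.9, rounded up to 50, so 100 in total.

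This reproduces the stated 100. The present point does not touch it. The literature comparison has no stated figure to reproduce.

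**2. What the literature comparison would estimate.** For any group of DT-arm patients,

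observed mean − literature value = effect of following or departing from advice + case-mix difference + background-care difference + sampling error.

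A test against the literature value tests the sum of the first three terms. The article's own text says that the case-mix term is often not zero.

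**3. Illustration of the size.** Assumptions, none of them in the article: a one-sample t test against a fixed literature value, two-sided 0.05, true effect zero, and a case-mix offset of b SD. Then the noncentrality is δ = b√n with n − 1 degrees of freedom, and

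P(reject) = P(T > t_crit) + P(T < −t_crit), where T is noncentral t with parameter δ.

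The value n = 50 is the planned size of one arm. The value n = 25 stands for the case where only half of that arm has departures; the true number is unknown.

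| Offset b (SD) | δ, n = 50 | Rejection, n = 50 (t_crit 2.010) | δ, n = 25 | Rejection, n = 25 (t_crit 2.064) |
|---|---|---|---|---|
| 0 | 0 | 5.0% | 0 | 5.0% |
| 0.1 | 0.707 | 10.7% | 0.5 | 7.7% |
| 0.2 | 1.414 | 28.4% | 1.0 | 16.1% |
| 0.3 | 2.121 | 54.8% | 1.5 | 30.2% |

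A normal approximation gives slightly higher values (10.9%, 29.3% and 56.4% at n = 50).

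**4. Which comparator serves which question.**

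| Question | Comparator in the article | Can TAU serve? |
|---|---|---|
| Does DT care increase the number reaching the 37% goal? | TAU, randomised | Yes, and it is planned |
| Does DT care change PGIC and the pain and psychological measures? | TAU, by mixed model for repeated measures | Yes, and it is planned |
| Does DT care change the individual NCD risk factors? | Secondary outcomes; no test named for them specifically | Yes |
| What follows when a clinician departs from DT advice? | Literature expectations | No: TAU clinicians receive no DT advice, so departure is undefined there, and it arises after randomisation |

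**The case against.** The strongest reply is that a reader might infer that the literature benchmark replaces the randomised control, or that case-mix differences will pass for DT effects. The article does not support either reading. The 37% goal, PGIC and the listed secondary efficacy measures are all compared between DT and TAU; the literature sentence adds an analysis and removes none. This part of the objection stands in full.

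A reader might also infer that TAU is the obvious comparator left unused for the departure analysis. It is not. Departure from DT advice has no meaning in TAU, and setting DT-arm patients selected by departure against the TAU arm would not be a randomised contrast. This stands too.

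Calling the benchmark circular would also go too far. Patients' measured risk factors are real observations and do not come to match published values because the advice drew on them. The sources overlap; the circularity is partial.

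Next, testing published guidelines on a heterogeneous population is a stated secondary objective, so a gap between this sample and the literature is partly what is being studied. That justifies showing the literature values. It does not justify a P value attributed to clinician variance, because the gap cannot be split into its components.

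Finally, the sentence could be implemented with individualised or covariate-adjusted expectations, a detail that an article may leave to fuller documents. That would reduce the bias from measured case mix, but differences in background care and unmeasured characteristics would remain. The choice of comparator is already stated.

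**Conclusion.** The concern holds in a limited form. The article commits to a statistical comparison against a benchmark that, on its own description of the patients, may not represent them, and that shares sources with the DT. A P value from it cannot be read as evidence about following or departing from DT advice. The DT versus TAU efficacy tests and the sample size are unaffected.

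The size cannot be stated from the document. The 11%, 28% and 55% figures are correct arithmetic under an assumed one-sample test of all 50 DT participants with assumed offsets of 0.1, 0.2 and 0.3 SD; they are not properties of any analysis that the article specifies.

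A related gap is worth closing at the same time. The individual NCD risk factors are secondary outcomes, but Statistical Methods spells out the DT versus TAU test only for PGIC and the pain and psychological measures. General remarks there about change scores by arm suggest that the same comparison is intended for other variables, but the risk factors are not named.

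This is an inexpensive improvement to a supportive analysis, not a flaw in the main design.

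**What to change.** Reword the one analysis as follows:

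1. Literature values are shown as descriptive context, without P values.
2. Clinician concordance with and variance from DT recommendations, and outcomes by concordance, are reported within the DT arm only, adjusted for baseline risk, and labelled non-randomised and exploratory. Baseline adjustment will not remove confounding by the clinician's reasons for departing, so the label matters.
3. The randomised DT versus TAU comparison is named as the inferential test for the NCD risk factors listed as secondary outcomes in Enrollment Procedures.

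The cost is a wording change. The data are already planned and the sample size does not move. The downside is that the literature benchmark loses its P value, and the departure analysis can then generate hypotheses for algorithm refinement but not confirm them.

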### Validation Study Material and Methods

#### Overview

All eligible participants will be provided sufficient details on the study so that they can provide informed consent prior to enrollment. This process will include a complete discussion of the study’s purpose, the study procedures, and the risks and benefits of participation. The risk discussion will include the risks and benefits of the use of AI for health care. All study data collected will be kept confidential and securely stored. All personal identification will be removed from the study data. Personal identifiers will be available to treating providers. Participation in this study is completely voluntary, and participants can withdraw at any time. The decision to participate in this study will not affect access to care. All treatment decisions will be made by the patient’s provider only. This study will conform to all international standards covering human subjects for this research project.

This study will be approved through the Institutional Review Board (IRB) of Brigham and Women’s Hospital in Boston and registered on ClinicalTrials.gov. The health care providers participating in this validation study will identify and sequentially include sufficient patients to validate this process. An effort will be made to include a diverse group of enrollees to allow for a subgroup analysis of the impact on decision-making in the biopsychosocial and personalized medicine. The potential participants will be new patients in their practice identified as having one of the NCDs that are being targeted in this study. The potential participants will be screened for both inclusion and exclusion criteria listed below. If found to be eligible, the personal smartphone of the identified participants will be polled using SMS text messages to determine interest. Interested individuals will be provided the study app and questionnaires associated with their provisional diagnosis. If the screening questionnaires are compatible with an NCD diagnosis, secondary questionnaires will be transmitted through the study app and an appointment will be made for confirmation of the diagnosis using the criteria listed in Textbox 2. After the confirmation of the diagnosis, each participant will be evaluated by a multidisciplinary team that will include the treating provider, a psychologist, and a physical therapist. After informed consent and sufficient instruction, the participants will be formally enrolled and treatment will begin. Relevant outcomes such as improvement in activity duration and frequency, as well as response to automated messaging, will be tabulated. Figures 4 and 5 illustrate the clinical pathways that will be implemented in this clinical trial of an NCD-focused DT, along with the feedback loops that will be used to refine the validity and increased accuracy of the DT toward being able to support a biopsychosocial personalized medicine at the level of N-of-1. The eligibility criteria are listed in Textbox 2.

Textbox 2.Inclusion and exclusion criteria.

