## Methods

### Validation Methodology for a DT NCD

This proposed study will use the smartphone (iOS and Android) and MobileNetrix as the health management systems platform for a patient DT NCD study. A HIPAA-compliant DT Health Management App will be created, supported by AI and computational analysis. The administrative portal will automatically poll each participant after being identified as a candidate based on validated criteria of having one of the NCDs studied in this protocol. The 3 NCDs that will be included are (1) cardiovascular disease, (2) type II diabetes (non–insulin dependent), and (3) chronic obstructive pulmonary disease.

Candidates will be screened through a 2-step evaluation process. After informed consent is received, the participants will be invited to download the study app. Following a successful app enrollment, a screening questionnaire specific to the provisional diagnosis will be sent through the study app that will contain a link to a designated questionnaire. Once complete, if the individual is found to qualify for the study through the screening questionnaire, an appointment will be made for a comprehensive evaluation to confirm the diagnosis and related risk factors. Table 3 details the screening process for each NCD.

**Table 3. T3:** Screening process for specific noncommunicable diseases.

NCD^a^ diagnosis	Screening questionnaire	Confirmatory evaluation
Cardiovascular disease	AHA PREVENT^b^ risk calculator [86]	Laboratory and physical exam: diabetes (%), current smoking (%), mean total cholesterol (mg/dL), mean systolic blood pressure (mm Hg) [87]
Type II diabetes	Diabetes Risk Score Questionnaire [88]	Fasting blood glucose >126 mg/dL, 2-hour OTT^c^ blood glucose >200 mg/dL, HbA_1C_^d^>6.5% [89,90]
COPD^e^	CDQ^f^ questionnaire [91]	Postbronchodilator spirometry ratio of FEV_1_/FVC^g^ of less than 0.70 confirms the presence of persistent airway obstruction and COPD [92]

a Noncommunicable disease.

b American Heart Association Predicting Risk of Cardiovascular Disease Events

c Oral tolerance test.

d Hemoglobin A1C.

e Chronic obstructive pulmonary disease.

f COPD diagnostic questionnaire.

g FEV_1_/FVC: forced expiratory volume in 1 second to forced vital capacity.

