**Inclusion criteria**
Personal smartphone (either Android or iPhone iOS).Clearance from the primary care provider.At-risk noncommunicable disease and confirmed by in-person evaluation.Willingness to participate.No contraindications to participating in treatment recommendations.

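### Informed consent comes before the study app in one Methods section but after the app, questionnaires and confirmatory visit in another, so a site following the second would collect study-app data before consent

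*Protocol article*

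**What the plan says.** Three sections of the protocol article describe how a candidate moves from identification to enrolment.

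**Validation Methodology for a DT NCD.** The administrative portal polls identified candidates. Consent comes next: "After informed consent is received, the participants will be invited to download the study app". Screening runs inside the app: "Following a successful app enrollment, a screening questionnaire specific to the provisional diagnosis will be sent through the study app". For those who qualify, "an appointment will be made for a comprehensive evaluation to confirm the diagnosis and related risk factors".

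**Overview, under Validation Study Material and Methods.** Providers identify new patients and check them against the inclusion and exclusion criteria. Then: "If found to be eligible, the personal smartphone of the identified participants will be polled using SMS text messages to determine interest". The next step depends on interest alone: "Interested individuals will be provided the study app and questionnaires associated with their provisional diagnosis". Secondary questionnaires go out through the app, an appointment is made to confirm the diagnosis, and a multidisciplinary team evaluates the participant. Consent appears only after all of this: "After informed consent and sufficient instruction, the participants will be formally enrolled and treatment will begin". The opening paragraph of the same Overview says that eligible participants will be informed so that they can consent before enrolment, and that the consent discussion will cover procedures and risks.

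**Enrollment Procedures.** The SMS poll is described with a different purpose: "They will be sent a poll using an SMS text messaging–based survey app for eligibility for in-person evaluation".

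Textbox 2 lists as an inclusion criterion: "At-risk noncommunicable disease and confirmed by in-person evaluation". Willingness to participate is another.

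**The concern.** Whether consent precedes the study app and its questionnaires should have one answer in a protocol. Here it has two, and both are written as instructions a site could follow. The app and its questionnaires are study procedures, not routine care. Study Risks itself names a breach of participants' data and discomfort while completing questionnaires as risks of taking part. If the Overview order is followed, candidates meet both risks before the discussion that is meant to explain them.

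There is also a reporting consequence. The numbers consented, and consented but not enrolled, depend on which section a site follows, because screen failures occur after consent in one order and before it in the other.

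**Working it through.** No arithmetic applies. The check sets the two step orders side by side and asks whether any other statement in the article reconciles them.

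| Step | Validation Methodology | Overview |
|---|---|---|
| Candidate identified | 1 | 1 (with a criteria check) |
| Poll | 2 | 2 (on interest) |
| **Informed consent** | **3** | **7 (first mention in the sequence)** |
| Study app provided | 4 | 3 (with first questionnaires) |
| Screening questionnaire | 5 | 3 |
| Secondary questionnaires | not named as a step | 4 |
| In-person confirmation | 6 | 5 |
| Further evaluation | 7 (added risk factors) | 6 (multidisciplinary team) |
| Formal enrolment, treatment | not stated as a step | 7, after consent |

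1. *Steps ahead of consent.* In the Overview, four steps stand between the interest poll and consent: the app with the first questionnaires, the secondary questionnaires, the confirmatory visit, and the team evaluation. In Validation Methodology none of these precedes consent. Both sections have a poll before consent, so the poll is not where they differ.

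2. *Does the general consent statement settle it?* The opening of the Overview asks for consent before enrolment. If enrolment means the formal enrolment at the end of the Overview, that statement allows everything up to that point to happen first. If it means enrolment in the app, it agrees with Validation Methodology. It fits either order and so decides nothing.

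3. *Is a two-stage consent described?* One consent for screening and a second for the trial would reconcile the sections. No section mentions such a scheme.

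4. *What is affected at minimum?* The app and its questionnaires, because their status as study procedures is clear from the text. The confirmatory tests may or may not be routine care, so the point does not rest on them.

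**The case against.** The strongest reply is that the Overview sentence lists what must be in place before enrolment and does not say that consent is first sought at that late stage. Validation Methodology gives the timing expressly and could be taken to govern. The study is also subject to ethics approval, and the Overview refers to a figure of the clinical pathways that the text at hand does not show. That reading is possible, but it does not remove the problem. The Overview is written step by step, names no earlier consent, and gives the app to anyone interested. A site working from it cannot tell that consent should already have been taken.

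Other parts of the reply stand, and they limit what a reader might infer:

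- *That the eligibility rule is circular.* The first check precedes the in-person visit that Textbox 2 requires. But the article speaks of potential participants, a provisional diagnosis and a two-step evaluation, and willingness cannot be known before an interest poll. The early use of eligible reads naturally as provisionally eligible. This is loose terminology.
- *That the SMS poll descriptions conflict outright.* Enrollment Procedures concerns eligibility for the next visit, not for the trial. It can largely be reconciled with a poll of interest, though the wording should agree.
- *That baseline efficacy data would be gathered before consent and lost.* Statistical Methods delivers the efficacy instruments through REDCap, with a baseline time point for all but the global impression of change. Nothing places that baseline before consent.
- *That study-driven tests such as spirometry are done before consent.* Candidates are new patients already identified as having one of the conditions. Table 3 lists confirmatory criteria without saying that the tests fall outside routine care.
- *That at least 115 people would be exposed.* That figure is the recruitment target in Statistical Methods, not a count of people screened or of people handled under the Overview order.

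**Conclusion.** The contradiction on the timing of consent is real and should be corrected before recruitment starts. Validation Methodology places consent before the app and screening questionnaire. The Overview, followed as written, places the app and both rounds of questionnaires before it. The consequence is conditional: it arises at a site that works from the Overview, and not at one that works from Validation Methodology. Its size is best stated as four steps ahead of consent in one order and none of those four in the other. The number of people affected cannot be estimated from the article.

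The conclusion assumes only that the Overview is meant as a sequence, as its wording indicates, and that the unseen figure and any fuller protocol do not override it. It does not touch the sample size, the power calculation or any planned analysis. The early use of eligible and the two descriptions of the poll are secondary matters of clarity.

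**What to change.** Use the order already given in Validation Methodology and bring the other sections into line.

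- In the Overview, say that informed consent is obtained once interest has been expressed and before the study app or any questionnaire is provided.
- In the later Overview sentence on formal enrolment, replace consent with confirmed eligibility as the condition, and keep the instruction step that the article states there and in Enrollment Procedures.
- In the Overview, call the first criteria check provisional eligibility, since in-person confirmation and willingness are established later.
- Give the SMS poll the same stated purpose in the Overview and in Enrollment Procedures.

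If the sponsor does intend a two-stage consent, describing it explicitly would also resolve the conflict, provided the first stage precedes the app and questionnaires.

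The cost is a few sentences in the protocol and the ethics submission. The article describes ethics approval as still to come and expects recruitment by June 2026, so on its own timetable the change can be made beforehand. No visit, test or analysis is added. The small downside is that some people will consent and then fail screening, and the participant flow should count them as such.
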